## Methods

### Study design

This will be a 52-week, single-blinded, two-arm RCT consisting of a supervised and structured multi-component exercise programme in combination with a daily nutritional supplement. Men treated with ADT will be randomised to either an intervention consisting of a multi-component exercise programme and a daily protein-, calcium- and vitamin D-enriched supplement (*n* = 51) or a usual care control group (*n* = 51). Men allocated to usual care will not receive a placebo drink as typical ingredients used to develop a placebo drink (e.g. maltodextrin as a food additive) have the potential to alter blood glucose levels and muscle mass. A factorial 2 × 2 trial will not be conducted for several reasons: (1) the large sample size that would be required to detect an interaction and (2) findings from previous research in older adults which indicates that the benefits of exercise training on musculoskeletal health require adequate nutrition (e.g. dietary calcium > 1000 mg/day) [38]. This study will not evaluate whether the combination of protein, calcium and vitamin D with exercise training is more effective than either of these treatments alone, but will determine if combining the two approaches is effective for improving multiple health outcomes. This trial will be managed by the Institute for Physical Activity and Nutrition at Deakin University. The study has been approved by the Human Research Ethic Committees at Deakin University (HREC 2013-184) and Alfred Health (Project No: 455/15) and is registered with the Australian and New Zealand Clinical Trials Registry (ACTRN12614000317695). A summary of trial resgistration data and compliance with SPIRIT guidelines are shown in Additional files 1 and 2, respectively.

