### Sample size calculation

The sample size calculations are based on our previous research in healthy and ADT-treated men. The mean (standard deviation (SD)) annual loss in femoral neck, hip and spine BMD in ADT-treated men was 3.0% (4.5), 2.6% (2.8) and 3.9% (3.0), respectively [14]. Our previous exercise trials in healthy older men have shown that 12 months of training can increase spine aBMD by 1.5–2.0% (SD 2.9) and hip aBMD by 1.2–1.8% (SD 2.8) [39, 55]. We estimate a conservative net difference in aBMD in favour of the intervention of ~ 3.5–4.0% at the hip and spine. Based on these estimates, 29 men in each group will provide 90% power (*P* < 0.05, two-tailed) to detect a difference of this magnitude (assuming a SD of 4.0). A net benefit of this magnitude is clinically relevant as there is evidence that a 1–2% gain in aBMD translates into a 7–14% reduction in fracture risk [36, 93]. For pQCT bone measures, radial and tibial cortical area decreased by 11.5% (8.8) and 12.5% (7.4), respectively, over 12 months in ADT-treated men [14]. While few long-term trials have examined the effect of exercise training on pQCT bone geometry in older men, several intervention trials in older adults have shown that a targeted, weight-bearing, impact-exercise programme can have beneficial effects on cortical bone [94, 95]. Assuming that the proposed intervention can half the rate of loss in cortical area, we estimate that we will require 39 men per group (SD 8.0; 90% power, two-tailed, *P* < 0.05). Based on a previous study and a meta-analysis showing that ADT is associated with an average 7.7% gain in fat and a 2.8% loss in lean mass over 3–12 months [96, 97], and that exercise training can prevent the gain in FM and increase (1–5%) or preserve LBM relative to usual care in men on ADT [30, 32], we estimate a sample size of 24–32 in each group will be required to observe a preservation in LBM and FM in the intervention group vs. usual care (90% power, two-tailed, *P* < 0.05). Assuming a conservatively projected 30% dropout, an estimated sample size of 51 men per group (102 in total) will be required. Based on previous studies in ADT-treated men focussing on a number of our secondary outcomes [32, 37, 98], we estimate that we will have sufficient power (80–90%, *P* < 0.05, two-tailed) to detect the following intervention effects: 20–40% for muscle strength; 8–22% for functional capacity; 4 points for fatigue (FACT-F), 15% for fasting plasma glucose and 14% for serum IL-6 and 20% for CRP. We will also have sufficient sample to detect a clinically meaningful difference of 0.5 SD in the Assessment of Quality of Life 8D questionnaire (AQoL-8D) and 9 points on the FACT-P (disease-specific QoL).

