
### Statistical analysis

Primary analyses will be conducted on an intention-to-treat basis using STATA statistical software (STATA, College Station, TX, USA). Per-protocol analysis will also be performed by including all participants who are at least 66% compliant to the exercise (two of three sessions per week) and 80% compliant to taking the supplements. Initially, descriptive statistics will be computed to compare the intervention and usual-care groups on background variables and baseline measures. All data will be screened for outliers and the normality of the distribution of all data will be assessed using Kolmogorov-Smirnov tests, with skewed data log transformed prior to analysis. Linear mixed models with random effects will be used to evaluate the effects of the intervention compared to usual control. Potential covariates to be included will be: age, duration of ADT use, other chronic conditions, change in medication and change in habitual physical activity or diet. Where possible, we will obtain endpoint measures from all withdrawals and include all randomised subjects in the final analysis. For participants who are lost to follow-up, missing data will be handled with multiple imputation, with subsequent sensitivity analyses to evaluate the effect of potential non-random attrition. Baseline measures and changes in outcome variables will be presented as means ± SD or 95% confidence intervals. A significance level of *P* < 0.05 will be adopted for all statistical tests.

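### The statement that the sample suffices to detect 0.5 SD on the AQoL-8D is not supported by the plan's stated inputs: unadjusted power is about 55% at 36 completers per group and 71% with all 51

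*Protocol article*

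**What the plan says.** All the inputs are in the Sample size calculation section of the protocol article. For aBMD, "29 men in each group will provide 90% power (*P* < 0.05, two-tailed) to detect a difference of this magnitude (assuming a SD of 4.0"), where the difference is about 3.5–4.0%. For cortical area, with the rate of loss halved from 11.5% and 12.5%, "we estimate that we will require 39 men per group (SD 8.0; 90% power, two-tailed, *P* < 0.05"). The total follows: "Assuming a conservatively projected 30% dropout, an estimated sample size of 51 men per group (102 in total) will be required".

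For several secondary outcomes the section then says "we estimate that we will have sufficient power (80–90%, *P* < 0.05, two-tailed) to detect the following intervention effects". The next sentence covers quality of life: "We will also have sufficient sample to detect a clinically meaningful difference of 0.5 SD in the Assessment of Quality of Life 8D questionnaire". It gives no power figure, does not say whether the SD is that of the score or of its change, and gives no correlation between visits.

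Table 2 lists the AQoL-8D at baseline, 26 and 52 weeks. Under Statistical analysis, "Linear mixed models with random effects will be used to evaluate the effects of the intervention compared to usual control". That section also seeks endpoint data from men who withdraw, includes everyone randomised, and imputes the remaining missing values.

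**The concern.** An effect stated in SD units carries its own scale, so its unadjusted power can be computed without any outside figure. The article sizes the trial at 39 completers per group to detect a difference of 0.75 SD (6.0/8.0) with 90% power. Required sample size rises with the inverse square of the standardised effect, so 0.5 SD at the same power needs roughly 39 × (0.75/0.5)² = 88 per group. It is therefore surprising that the same trial is called sufficient for 0.5 SD.

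Health-related quality of life is a declared secondary aim, and the article calls 0.5 SD clinically meaningful. If readers accept that the trial is large enough, they may take a non-significant AQoL-8D result as ruling out a meaningful benefit. On the unadjusted figures, a true 0.5 SD effect would be missed about 45% of the time.

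**Working it through.** **Inputs.** Two-tailed alpha 0.05; 51 per group; 30% dropout; effect 0.5 SD. All are from the Sample size calculation section. The 80–90% power standard is taken from the sentence before the AQoL-8D claim. Completers: 51 × 0.70 = 35.7, about 36 per group.

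**Formula.** With d = difference/SD, n per group ≈ 2(1.960 + z)²/d², where z = 0.842 for 80% power and 1.282 for 90%. The exact t-test adds about one man per group. The t-test results are used below.

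**The plan's own figures.**
- aBMD, 90%: d = 3.5/4.0 = 0.875; t-test n = 28.4, so 29. Stated: 29.
- Cortical area, 90%: d = 6.0/8.0 = 0.75 (6.0 is half of 12.0, the midpoint of 11.5 and 12.5); t-test n = 38.3, so 39. Stated: 39.

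**The same method at d = 0.5.**
- 80% power: 2(2.802)²/0.25 = 62.8; t-test 63.8, so 64 per group.
- 90% power: 2(3.242)²/0.25 = 84.1; t-test 85.03, so 86 per group.

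**Power delivered at d = 0.5**, approximately Φ(0.5√(n/2) − 1.960):

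| n per group | Normal approximation | t-test |
|---|---|---|
| 36 | 56% | 55% |
| 39 | 60% | 59% |
| 51 (no dropout) | 71% | 71% |

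The smallest difference detectable at 36 per group is 0.67 SD (80% power) or 0.77 SD (90%). At 51 per group it is 0.56 SD (80%).

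**Baseline adjustment at one visit, SD of the score.** The effective d is 0.5/√(1 − r²), where r is the baseline-to-52-week correlation (an assumption; none is given). For 80% power at 36 per group, 1 − r² must be at most (0.5/0.670)² = 0.557, so r is at least about 0.67. At 51 per group, 1 − r² must be at most (0.5/0.560)² = 0.797, so r is at least about 0.45. At 36 per group, power is 68% for r = 0.5, 74% for r = 0.6 and 83% for r = 0.7.

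**Baseline-adjusted mean of both follow-ups, SD of the score.** Assume the same r between every pair of visits. The variance factor is (1 + r)/2 − r². At 36 per group:
- r = 0.3: factor 0.56, power 80%.
- r = 0.5: factor 0.50, power 84%.
- r = 0.6: factor 0.44, power 88%.

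**SD of change.** Comparing changes gives 55% and 71% whatever r is. Adjusting for baseline as well gives d = 0.5√(2/(1 + r)). This reaches 80% at 36 per group only if 2/(1 + r) ≥ (0.670/0.5)² = 1.79, so r is at most about 0.12. At 51 per group the limit is (0.560/0.5)² = 1.255, so r is at most about 0.59. The thresholds of 0.67 and 0.45 therefore do not carry over to this reading.

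**The case against.** The strongest reply is that a t-test on completers is not the planned analysis. The article specifies mixed models on a measure taken three times. An effect averaged over 26 and 52 weeks with baseline adjustment could have about 80% power at 36 per group even with modest correlations. Some men who leave the programme may still return a questionnaire, so 36 is the pessimistic end. The AQoL-8D sentence names no power, so the 80% standard is inferred from its neighbour.

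Much of this stands. A reader might infer that the statement is simply false, or that 64 per group are needed whatever the analysis. The document does not support that, because it does not rule out a contrast and correlation under which 80% is reached.

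The reply does not supply the missing support, however. The article gives no correlation, contrast or SD type, and the baseline value is not among its listed potential covariates. Its other calculations that can be checked use the unadjusted method. Full retention gives only 71% unadjusted, and imputation does not restore lost information. A one-sided test with all 51 would reach 81%, but the article specifies two-tailed. As for the borrowed standard, 55% is hard to call sufficient under any usual one.

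A reader might also infer that the neighbouring claims for FACT-P, FACT-F, CRP and IL-6 are wrong. No SDs are given for them, so no error is shown.

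**Conclusion.** The claim of sufficiency is unsupported on the stated inputs. By the method that reproduces the article's 29 and 39, power for 0.5 SD is about 55% at 36 completers per group and 71% at 51, against a need for 64 per group at 80%. These figures assume an unadjusted two-sample comparison at two-tailed 0.05, with the power standard carried over from the preceding sentence. Reaching 80% depends on choices that the article leaves unstated: the type of SD, the contrast and the correlation.

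Severity is minor to moderate. The AQoL-8D is one of many secondary outcomes, the 51 per group does not derive from it, and neither the primary comparison nor recruitment is affected.

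**What to change.** Change the sentence in one of three ways:
- State the power delivered: about 55% unadjusted for 0.5 SD with about 36 completers per group, and 0.67 SD detectable with 80% power.
- Keep the claim, but give what justifies it: whether the SD is of the score or of change, whether the contrast is at 52 weeks or averaged over follow-up, whether baseline is adjusted for, and the assumed correlation with its source.
- Withdraw the claim.

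In each case, interpret the AQoL-8D result through its 95% confidence interval set against 0.5 SD, rather than by significance alone. The Statistical analysis section already allows changes to be reported with such intervals.

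The cost is a change of wording and a less favourable stated property. No patients are added and the analysis does not change.

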
### Statistical analysis

Primary analyses will be conducted on an intention-to-treat basis using STATA statistical software (STATA, College Station, TX, USA). Per-protocol analysis will also be performed by including all participants who are at least 66% compliant to the exercise (two of three sessions per week) and 80% compliant to taking the supplements. Initially, descriptive statistics will be computed to compare the intervention and usual-care groups on background variables and baseline measures. All data will be screened for outliers and the normality of the distribution of all data will be assessed using Kolmogorov-Smirnov tests, with skewed data log transformed prior to analysis. Linear mixed models with random effects will be used to evaluate the effects of the intervention compared to usual control. Potential covariates to be included will be: age, duration of ADT use, other chronic conditions, change in medication and change in habitual physical activity or diet. Where possible, we will obtain endpoint measures from all withdrawals and include all randomised subjects in the final analysis. For participants who are lost to follow-up, missing data will be handled with multiple imputation, with subsequent sensitivity analyses to evaluate the effect of potential non-random attrition. Baseline measures and changes in outcome variables will be presented as means ± SD or 95% confidence intervals. A significance level of *P* < 0.05 will be adopted for all statistical tests.

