### Usual-care control group

Participants allocated to usual care will receive ongoing care from their physician/specialist but will not receive additional education or access to exercise training or the protein-, calcium- and vitamin D-enriched nutritional supplement powder sachet. Due to current practice guidelines [40] and a pilot study we conducted in 31 men undergoing ADT for PCa in which 65% reported taking vitamin D supplementation (90% at least 1000 IU/day), all men randomised to usual care will receive 1000 IU vitamin D per day. There is no evidence that vitamin D alone (without calcium supplementation) at these doses can prevent bone loss in these men [40].

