### Measurements

All measures will be collected at baseline, 26 and 52 weeks. Additionally, 24-h food recalls will also be administered at 13 and 39 weeks to monitor any habitual fluctuations in dietary factors. With the exception of blood samples, 24-h food recalls and questionnaires, all data will be collected at Deakin University. Blood samples will be collected at an external commercial pathology clinic. The 24-h food recalls will be administered via telephone. Questionnaires will be completed by participants at home prior to each testing sessions (i.e. baseline, 26 and 52 weeks) and checked by the research staff during these face-to-face testing sessions. A summary of the proposed outcome measures is shown in Table 2. All participants will undergo all measures expect those specific to treatment allocation (i.e. compliance to the intervention). All data collected will be in a continuous format, aside from the outcomes from some of the questionnaires, which will be categorical in nature.

**Table 2 Tab2:** Summary of data collection

Variables	Data collection method	Data collection points		
		Baseline	26 weeks	52 weeks
Primary outcome measures				
Areal bone mineral density	DXA proximal femur and lumbar spine	x	x	x
Secondary outcome measures				
Bone structure and strength	pQCT scan at 4% and 66% radial and tibial site	x	x	x
Body composition	DXA total body and regional lean mass, fat mass and % body fat	x	x	x
	pQCT 66% radial and tibial muscle cross-sectional area and muscle density	x	x	x
Muscle strength	Chest press, leg press and seated row	x	x	x
	Grip strength	x	x	x
Functional capacity	30-s sit-to-stand	x	x	x
	Timed-up-and-go with cognitive task	x	x	x
	Four-square step test	x	x	x
	Berg balance scale	x	x	x
	Four-metre usual walk	x	x	x
	400-metre walk	x	x	x
Biochemistry and lipids	Overnight, fasted serum and plasma collection	x	x	x
Inflammatory markers	Overnight, fasted serum and plasma collection	x	x	x
Blood pressure	Automated measurement	x	x	x
Cognitive function	CogState Brief Battery computerised tests	x	x	x
	Rey Auditory Verbal Learning Test	x	x	x
	Trail Making Test (Part A and B)	x	x	x
	Digit Span Test	x	x	x
	National Adult Reading Test	x		
Health-related quality of life, fatigue and mood	Functional Assessment of Cancer Therapy-Fatigue questionnaire	x	x	x
	Functional Assessment of Cancer Therapy-Prostate questionnaire	x	x	x
	Assessment of Quality of Life 8D questionnaire	x	x	x
	Geriatric Depression Scale questionnaire	x	x	x

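### The secondary per-protocol comparison in effect sets adherers in the intervention arm against all controls, so it is biased if adherence is related to bone change

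*Protocol article*

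**What the plan says.** The Statistical analysis section puts intention-to-treat first: "Primary analyses will be conducted on an intention-to-treat basis". It then adds: "Per-protocol analysis will also be performed by including all participants who are at least 66% compliant to the exercise". The sentence goes on to explain the exercise threshold and join a second one to it: "two of three sessions per week) and 80% compliant to taking the supplements". No separate rule is given for the usual-care arm, and one significance level, P < 0.05, is set for every test.

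Other sections show what each arm can comply with. Under Usual-care control group, controls "will not receive additional education or access to exercise training or the protein-, calcium- and vitamin D-enriched nutritional supplement powder sachet", but "all men randomised to usual care will receive 1000 IU vitamin D per day". Under Study design, "Men allocated to usual care will not receive a placebo drink". The Compliance section defines exercise compliance as attendance at training sessions. The Measurements section treats compliance as specific to allocation: "All participants will undergo all measures expect those specific to treatment allocation (i.e. compliance to the intervention".

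**The concern.** Membership of the per-protocol set depends on behaviour after randomisation that one arm has no opportunity to show. Filtering the intervention arm on a year of attendance and supplement use, with no equivalent filter on controls, gives up the comparability that randomisation provided. Men who keep attending may differ in health, function or activity from men who stop, and those differences may themselves go with bone loss.

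At stake is how a positive per-protocol result would be read. The article does not label this analysis supportive or descriptive. With 30% dropout projected, the intention-to-treat estimate may be diluted. A per-protocol result below P < 0.05 could then be taken as evidence of efficacy when part or all of it is selection.

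**Working it through.** **Who can qualify.** The two criteria are joined by 'and'. Two of three weekly sessions is 66.7%, which agrees with the 66% threshold.

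- Exercise, 66%: can be met in the intervention arm; controls have no programme and no attendance to count.
- Supplements, 80%: sachet and vitamin D tablet in the intervention arm; vitamin D 1000 IU/day only in controls. The Compliance section counts returned sachets and tablets without naming an arm, so it is unclear whether controls' tablets are counted.

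The workable reading filters the intervention arm and keeps all controls. Screening controls on vitamin D alone would still select the arms on different behaviour.

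**The plan's own figure.** The Sample size calculation section uses a difference of about 3.5–4.0 points in aBMD, SD 4.0, 90% power and two-tailed P < 0.05, and states 29 per group. With a difference of 3.5, the normal approximation gives 28 and the exact noncentral t gives 29, so the figure reproduces. The SD of 4.0 and the effect of 3.5 are used below.

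**Bias formula with no true effect.** Let p be the compliant share, and let the gap be the difference in untreated 12-month aBMD change, would-be adherers minus non-adherers. By randomisation, controls contain both types in the same proportions.

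- Adherers' mean: A
- Control mean: p × A + (1 − p) × N
- Difference: (1 − p) × (A − N) = (1 − p) × gap

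The document gives neither p nor the gap. The assumed ranges are p = 0.5–0.7 and gap = 1–2 points. False-positive rates come from 4,000 simulated trials with 36 men per group (51 × 0.7 = 35.7), SD 4.0, no true effect and no covariate adjustment.

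| p | gap | (1 − p) × gap | simulated difference | false positives |
|---|---|---|---|---|
| 0.5 | 1 | 0.5 | 0.49 | 6.9% |
| 0.5 | 2 | 1.0 | 1.00 | 13.4% |
| 0.6 | 1 | 0.4 | 0.38 | 6.2% |
| 0.6 | 2 | 0.8 | 0.79 | 10.8% |
| 0.7 | 1 | 0.3 | 0.30 | 5.4% |
| 0.7 | 2 | 0.6 | 0.62 | 8.2% |

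Relative to the planned 3.5 points, 0.3/3.5 = 9% and 1.0/3.5 = 29%. In the same simulations the mean complier-average estimate lay between −0.05 and 0.01.

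**Second model as a check.** Let a latent adherence score correlate r with aBMD change, and keep the most adherent fraction f of 51 intervention men and all 51 controls. The bias is r × SD × φ(c)/f, with c = z(1 − f). At f = 0.6 (about 31 men against 51):

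- r = 0.1, 0.2, 0.3, 0.4: bias 0.26, 0.52, 0.77, 1.03 points
- type I error by normal approximation: 5.9%, 8.8%, 13.8%, 21.3%
- 10,000 simulated trials gave 5.2% at r = 0, 8.4% at r = 0.2 and 13.0% at r = 0.3

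Dividing the bias by 1 − f = 0.4 gives implied gaps of about 0.65, 1.3, 1.9 and 2.6 points. So r = 0.2–0.3 falls within the 1–2 point range and agrees with the table; r = 0.4 lies beyond it. At r = 0 the bias is zero.

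**Whether the plan repairs it.** The listed potential covariates are not tied to selection by adherence, and changes in medication, physical activity and diet arise after randomisation. Multiple imputation and the attrition sensitivity analyses deal with loss to follow-up, not with exclusion for low compliance.

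**The case against.** The strongest reply is that the analysis is secondary. Intention-to-treat is primary, endpoint data are sought from men who withdraw, and no efficacy claim is attached to the per-protocol set. That stands and limits the weight of the point.

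A second reply is that how controls enter the set is ordinary analysis-plan detail that a journal article may leave out. That is fair for a missing detail. But the article states the rule itself, and every workable reading of it selects the arms differently.

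A third reply is that the size is all assumption. That also stands. The 1.0 point and 13% figures come from the extreme corner (p = 0.5, gap = 2, half an SD). At the other corner the error rate is close to nominal. Adjustment for age, ADT duration and chronic conditions could remove some of the bias, and the eligibility criteria already exclude men doing regular resistance or impact exercise.

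A fourth reply is that a complier-average effect has its own bias, because it assumes no benefit below the threshold. Suppose the true complier effect is 3.5 and men below the threshold get half of it, 1.75. The estimate is then (0.5 × 3.5 + 0.5 × 1.75)/0.5 = 5.25 at p = 0.5, and (0.7 × 3.5 + 0.3 × 1.75)/0.7 = 4.25 at p = 0.7. Those overstatements, 1.75 and 0.75 points, exceed the per-protocol bias in the table at the same p. This is a good reason not to make it a mandatory replacement.

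A reader might also infer that the per-protocol set contains no controls. Literally, none of the 51 can meet the exercise criterion. But the same section describes evaluating the intervention against usual care, so an analysis without controls cannot be meant, and this is a matter of wording.

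**Conclusion.** The point holds for the secondary per-protocol analysis only. Its definition can be met in full only by intervention men, so in practice adherers are compared with all controls, and the estimate is biased to the extent that adherence is related to bone change. Under the assumed 50–70% compliance and 1–2 point gap, the bias is about 0.3–1.0 percentage points, 9–29% of the planned 3.5, with false positives of about 5–13%. The upper end only reaches the bottom of the 1–2% gain that the Sample size calculation section links to fracture risk.

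Three stronger conclusions are not supported. The primary result is not compromised, because it is by intention to treat. Bias in favour of the intervention is plausible but not established, because the document gives no data on adherence and bone change. Nor does the article say that the per-protocol result will be reported as proof of efficacy in compliers; that is a risk of misuse, not a stated plan.

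**What to change.** State that the 66% and 80% thresholds filter the intervention arm only and that all controls are kept. Label the comparison descriptive, and exempt it from the general P < 0.05 rule so that no efficacy conclusion is drawn from it.

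Beside it, add an adherence analysis that keeps all randomised men. One option is a complier-average causal effect with randomised arm as instrument and the same thresholds. As controls have no access to the programme, this is essentially the intention-to-treat difference divided by the compliant share. Report it with the caveat that it assumes no benefit below the threshold and overstates the effect if partial compliers benefit, and repeat it over lower thresholds as a sensitivity analysis. Inverse-probability weighting on baseline predictors of adherence is an alternative.

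The cost is a paragraph of analysis text, one further model with its sensitivity runs, and a wider interval than the per-protocol comparison. No new data are needed, and the Trial status section has recruitment still under way, so the change can be made before analysis.
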